## Abstract

**Background:**

Evidence demonstrates that measures are needed to optimise therapy and improve administration of medicines in care homes for older people. The aim of this study is to determine the clinical and cost effectiveness of a novel model of multi-professional medication review.

**Methods:**

A cluster randomised controlled trial design, involving thirty care homes. In line with current practice in medication reviews, recruitment and consent will be sought from general practitioners and care homes, rather than individual residents. Care homes will be segmented according to size and resident mix and allocated to the intervention arm (15 homes) or control arm (15 homes) sequentially using minimisation. Intervention homes will receive a multi-professional medication review at baseline and at 6 months, with follow-up at 12 months. Control homes will receive usual care (support they currently receive from the National Health Service), with data collection at baseline and 12 months. The novelty of the intervention is a review of medications by a multi-disciplinary team. Primary outcome measures are number of falls and potentially inappropriate prescribing. Secondary outcome measures include medication costs, health care resource use, hospitalisations and mortality.

The null hypothesis proposes no difference in primary outcomes between intervention and control patients. The primary outcome variable (number of falls) will be analysed using a linear mixed model, with the intervention specified as a fixed effect and care homes included as a random effect. Analyses will be at the level of the care home. The economic evaluation will estimate the cost-effectiveness of the intervention compared to usual care from a National Health Service and personal social services perspective.

The study is not measuring the impact of the intervention on professional working relationships, the medicines culture in care homes or the generic health-related quality of life of residents.

**Discussion:**

This study will establish the effectiveness of a new model of multi-professional clinical medication reviews in care homes, using novel approaches to recruitment and consent. It is the first study to undertake an examination of direct patient outcomes, together with an economic analysis.

**Trial Registration:**

ISRCTN: ISRCTN90761620

## Background

This trial is concerned with the management of medicines in care homes. In 2001 there were 528,000 registered beds in 27,480 general residential and nursing homes in the UK and by 2020 this is predicted to increase by 23% [1]. General Practitioners (GPs) have principal responsibility for the medical care of care home residents and, owing to the relatively high morbidity in this population, the size of the care home population has a major impact on their overall workload [2]. Care home residents are commonly the most infirm members of the primary care community with 82% of older people in care homes having long-standing illness and 48% having two or more chronic conditions [3]. The high level of morbidity in this population is associated with a high level of prescription medicines, with care home (residential and nursing) residents receiving an average of seven medicines [4,5]. A report by the National Care Standards Commission (NCSC) in 2004 suggested that care providers seek greater involvement of pharmacists in medicines management issues and that primary care should consider commissioning reviews of prescribing practice in care homes after they found that only 44% of care homes for older people met the national minimum standards on medication [3].

Evidence demonstrates that medicines management of residents in care homes for older people could be significantly improved [6]. Medication reviews for such patients have identified high proportions of patients receiving sub-optimal therapy, with the main medication error being the continuation of medication that is no longer required [7,8]. Other problems have been identified, such as prescribing medication to counteract side effects of other medication [9], or prescribing without monitoring [10] - the exact extent of these problems is unknown. Poor medicines management leads to therapeutic failure and influences the likelihood of adverse events, for example, increasing number of falls [11] or, in the case of certain drugs used in patients with dementia, reducing survival [12]. There have been a number of calls for measures to optimise therapy and to improve the administration of medicines in this context [13], with a multi-disciplinary approach to care recommended [14].

Although studies of pharmacist medication reviews in primary care have demonstrated pharmacists' ability to identify and resolve drug-related problems and reduce prescribing [15-17], these results have not been generalisable as they tended to use a small number of pharmacists. Studies that have used a larger number of pharmacists are usually confounded by lower quality relationships with prescribers and have failed to identify significant improvements in clinical outcomes [18-22], with one study identifying an increase in hospital admissions [23].

Pharmacist-led medication reviews in care homes have also demonstrated the ability to reduce the number of prescribed medicines, but failed to detect significant change in morbidity or mortality [7,24]. Zermansky *et al. *performed a Randomised Controlled Trial (RCT) on 661 care home residents [5]. One clinical pharmacist performed the medication reviews and made recommendations to the GP. After six months follow-up the number of medication changes in the intervention group had significantly increased and the number of falls was reduced, but no other patient benefits were detected.

Very few RCTs of pharmacist-led medication reviews in the UK have included an economic evaluation. The aim of most pharmacist medication review studies has been to improve patient treatment by altering medication, thus medication costs have been included in three RCTs which demonstrated favourable prescribing outcomes [5,15,17]. Furniss *et al's. *RCT in nursing homes considered the costs (using local figures) of all primary and secondary care contact for each resident. However, the authors reported that formal economic evaluation was not possible as healthcare professionals often visited patients not included in the study during their visits [7].

It is evident from the research available that pharmacists working in isolation have limited impact on patient orientated outcomes in care homes and have failed to demonstrate cost effectiveness. The aim of this RCT is to determine the clinical and cost effectiveness of a multi-professional team approach to medication reviews in care homes.

This novel model of medication review was developed by a Primary Care Trust (PCT) Medicines Management Team (MMT) in collaboration with GPs and after consultation with geriatricians. Within the NHS, PCTs are responsible for the care of approximately 500,000 patients within a local area, assessing need and commissioning care. The vast majority of care is commissioned from independent providers such as GP practices, Community Pharmacists, Dentists and other healthcare providers. All PCTs include a MMT who are responsible for managing prescribing budgets and prescribing systems, together with supporting primary care providers. Therefore, many PCTs employ pharmacists and technicians to work with GP practices to support prescribing and this often involves reviewing patients' medication. This activity is usually completed independently by the MMT and then interventions are agreed with the prescriber at a later date. By improving the management of medicines, the new model under evaluation is designed to deliver better health outcomes for care home residents and enhance the use of healthcare resources. The uniqueness of the model is the multi-professional team approach, involving pharmacists, pharmacy technicians and care home staff, as well as the GP(s) responsible for the medical care of residents. The multi-disciplinary team meet together to review and discuss the medications of care home residents. This model has the potential for wider implementation, but the effectiveness of this approach requires evaluation.

The clinical medication review involves consideration of patients' medical history, recent blood test results and current medications. Prior to the meeting the pharmacist will review patient data and prepare a list of recommended actions. The latter will be considered at the review meeting, with the pharmacist drawing on the expertise of the GP and care home staff. The medication review is designed to identify the high instances of inappropriate prescribing in care home residents[25], reduce the number of medication errors [4] and increase the frequency of monitoring. The majority of drug-related problems in care home residents relate to psychoactive medication [26] and therefore stopping these medications, combined with the other benefits of a clinical medication review in this population, is predicted to reduce falls [27]. The review meeting also offers the opportunity for generic medicines management issues at the home to be raised.

The objectives of the RCT are to determine the impact of the multi-professional medication review service (MMRS) on the number of falls and potentially inappropriate prescribing (number of drugs which match the Screening Tool of Older Persons Prescriptions (STOPP) criteria [28] at each data collection point). The trial will also examine the impact on medication costs, utilisation of health and social care resources, and mortality. The primary analysis is a direct comparison of the two groups: intervention and control. Analyses will essentially be at the level of the care home rather than the patient (see section entitled Clinical analysis).

## Methods

### Trial design

A cluster randomised controlled trial will be used and a flow chart outlining the study design appears in Figure 1. The project will involve care homes for older people (average age > 65 years) registered with a GP in the local area. Thirty care homes will be recruited to the trial: 15 in the intervention arm and 15 in the control arm. Intervention homes will receive a MMRS at baseline and six months, with final data collection at 12 months. Control homes will receive usual care (support they currently receive from the National Health Service (NHS)) with data collection at baseline and at 12 months. Following final data collection at the control homes, a MMRS can be implemented.

**Figure 1 F1:**
[figure not shown]
Flow chart of trial design.

The study has ethical approval from the NHS Norfolk Research Ethics Committee (REC reference 09/H0310/96).

### Recruitment

In the first instance, the GP practices responsible for the medical care of residents will be contacted by letter and accompanying information sheet to advise them of the study. It is expected that support and endorsement of the study by the Chairs of the Locality Prescribing Groups and the Primary Care Research Network will assist in promoting the study. A follow-up phone call from a researcher will establish expressions of interest and arrange a face-to-face meeting to explain the study in more detail.

Following agreement from GPs to include the MMT in the service responsible for the clinical care of care home residents, care homes will be approached for their consent. It is expected that care homes will be more willing to consider participation if they know that the GP practices have already given their consent to taking part in the study. A similar process of contact will be used, i.e. initial contact by letter and information sheet, with follow-up phone call and face-to-face meeting. Consent will be sought at the care home management level, rather than individual resident level. The process of obtaining consent from GPs and care home managers is in line with current practice for medication reviews in care homes.

The intervention is at the level of the home and, following standard practice, all residents in the home will have their medication reviewed. A leaflet will be given to residents (or their relatives) informing them about the study.

### Eligibility of care homes

There are more than 130 care homes in the PCT area, but after all exclusions it is predicted there will be approximately 65 care homes eligible for participation.

In order to take part the care homes must be for older people (average age >65 years) and have been registered with the Care Quality Commission (CQC) for at least six months. Care homes specifically for people (of all ages) with learning disability, sensory impairment, mental health problems, physical disabilities and alcohol dependence will be excluded. Care homes will also be excluded if they have received a medication review service from the PCT in the last 6 months, if they receive the services of a community geriatrician or if they are subject to investigation of the safeguarding of vulnerable adults.

As consent is being sought at the care home level, residents who self-medicate will be excluded. Those residents who are in the home for respite care will also be excluded.

### Allocation to treatment

Care homes will be segmented according to their resident mix (three categories: care home, care home with nursing, care home with residential and nursing beds) and size (i.e. number of beds - again three categories: small, medium and large). Recruitment will then proceed in 'waves'.

In the first wave a relatively homogeneous block of homes with approximately 30 residents will be approached as this represents the optimum number of residents for delivery of the intervention. For the second and subsequent waves, the homes to be approached will be decided purely on the basis of facilitating recruitment. For practical (i.e. workload) reasons, consenting homes will be allocated to intervention or control sequentially after consent is obtained using minimisation. This strategy has the advantage of achieving approximate balance between treatment groups with respect to stratifying factors (here resident mix and size) whilst allowing the practical advantage of being able to make allocations sequentially as homes are recruited, rather than having to wait for blocks to accumulate. Recruitment will cease once approximately 900 residents have been recruited.

### Sample size estimation

Previous research suggests that medication review services can reduce the average number of falls per patient over a 6 month period by 0.59 (confidence interval: 0.49 to 0.70), with a variance per patient of four [5]. This study was conducted in a similar setting and therefore we estimate the baseline frequency of falls to be similar (approximately 1 per resident per six months). Using the lower end of this confidence interval, 261 patients in each group would be required to detect this difference with 80% power and at the 5% level of significance. Assuming the intra-cluster correlation coefficient is 0.02 then in an average home (30 residents) this sample size needs to be multiplied by 1.58 [29] (the design effect allowing for clustering). Thus a total of 824 patients (412 in each group) will need to be recruited from approximately thirty homes. In recruiting 30 homes with an average of 30 residents this will allow for 10% losses to follow-up.

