### Clinical analysis

The null hypothesis is that there will be no difference in primary outcomes between intervention and control patients. All data will be stored on a relational database, which will assist with ongoing management. Data will then be arranged for further analysis in other programs including Microsoft Excel^©^, GenStat and SPSS^©^. The patient population will be characterised using the appropriate descriptive statistics, with medicines categorised according to those described within the British National Formulary (BNF) and medical problems classified according to the World Health Organisation International Classification of Diseases (ICD-10). Descriptive analysis of pharmaceutical care issues and action points in intervention patients will be recorded.

In this paper we are restricting ourselves to a description of our primary analysis, which is a direct comparison of the two groups: intervention and control.

For the following outcome variables - number of falls, emergency hospital admissions and deaths - the total number of events in each care home will be aggregated, along with total resident days 'at risk' in the same period. The events data will be analysed by fitting a hierarchical generalized linear mixed model to them. The basic generalized linear model used will be a log-linear model with Poisson error and log ('at risk' days) as an offset. The care homes themselves will be represented as random effects. Fixed effects in the model will be the intervention itself, the home size (small, medium, large), and resident-type (a two-level factor: residential care vs nursing care). The fact that 'mixed' homes have both types of resident means that the event-counts and 'at risk' days counts will have to be aggregated separately for each type in these homes. The standard error associated with the estimate of the effect of the intervention will be adjusted as necessary to take account of the cluster design. These models will be fitted in the GenStat statistical package using residual maximum likelihood (REML).

It is to be noted that the above analyses are essentially at the level of the care home rather than the patient. There are no identified covariates for the primary analysis. However, exploratory analyses may be conducted at the patient level, should a case emerge for including patient-level covariates in a secondary analysis.

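### The falls sample size takes 0.49 as a cautious absolute reduction, but its inputs do not cohere; the quoted 0.59 (0.49 to 0.70) is probably a rate ratio, and then 80% power at the cautious end is not delivered

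*Protocol article*

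**What the plan says.** All the inputs are in the protocol article. Under Sample size estimation, earlier research is said to "reduce the average number of falls per patient over a 6 month period by 0.59 (confidence interval: 0.49 to 0.70"). The variance is put at four for each patient, from the same source (reference [5]). The same paragraph adds: "we estimate the baseline frequency of falls to be similar (approximately 1 per resident per six months"). The lower limit of the interval is then taken as the difference to detect: "Using the lower end of this confidence interval, 261 patients in each group would be required to detect this difference with 80% power", at a 5% significance level. An intra-cluster correlation of 0.02 and 30 residents per home give a design effect of 1.58, hence 412 per group and 824 in total.

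The Background gives the size of the source trial (also reference [5]), which "performed a Randomised Controlled Trial (RCT) on 661 care home residents" with six months of follow-up. Under Clinical analysis, falls are to be analysed with a "log-linear model with Poisson error and log ('at risk' days) as an offset", so the estimated effect will be a rate ratio.

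**The concern.** Taking the limit of an interval nearest to no effect is a cautious way to plan. On a difference scale that is the lower limit, 0.49. On a ratio scale it is the upper limit, 0.70, and 0.49 is the largest effect in the interval. The scale of 0.59 therefore decides whether the plan's choice was cautious or optimistic.

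The printed interval is also far too narrow for a mean difference when the variance is four and the trial had 661 residents. Falls is a primary outcome, and this paragraph is the article's only justification of sample size. If the scale was misread, readers would believe the trial had 80% power for the weakest effect compatible with the earlier evidence when it did not.

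**Working it through.** **Inputs.** Effect 0.59 with interval 0.49 to 0.70, variance 4, baseline about 1 fall per resident per six months, 80% power, 5% level, design effect 1.58 and 412 per group, all from Sample size estimation; 661 residents in the source trial, from the Background. Assumed: equal arms in that trial (330.5 each), a 95% interval and two-sided testing (one-sided would give 206 per group, not 261).

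**1. The plan's figure reproduces.** n per group = 2 × (1.96 + 0.8416)² × 4 / 0.49² = 261.5, against the stated 261. Design effect = 1 + 29 × 0.02 = 1.58. Then 261 × 1.58 = 412 per group, or 824 in total. So 0.49 was entered as an absolute difference in means.

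**2. Interval for a mean difference of 0.59 with variance 4.** SE = √(4 × 2 / 330.5) = 0.156. Half-width = 1.96 × 0.156 = 0.305. Interval 0.29 to 0.89. The printed half-width is about 0.105, which would need a variance of about 0.47.

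**3. Interval for a rate ratio of 0.59 with Poisson variance.** Expected falls are 330.5 in controls and 0.59 × 330.5 = 195 under intervention. SE of the log ratio = √(1/330.5 + 1/195) = 0.0903. Interval 0.494 to 0.704, which rounds to the printed one. The SE implied by the printed limits is ln(0.70/0.49) / 3.92 = 0.0910.

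**4. How far this discriminates.**

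| Reading | Variance | Baseline | 95% interval |
|---|---|---|---|
| Difference | 4 | any | 0.29 to 0.89 |
| Difference | Poisson | 1 | 0.46 to 0.72 |
| Difference | Poisson | 0.8 | 0.48 to 0.70 |
| Ratio | Poisson | 1 | 0.494 to 0.704 |
| Ratio | 4 in both arms | 1 | 0.39 to 0.90 |
| Ratio | negative binomial, k = 3 | 1 | 0.43 to 0.81 |

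The Poisson ratio at the plan's own baseline fits best. Variance 4 fits on neither scale.

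**5. Power if 0.59 is a ratio (six-month falls, baseline 1).** Effective n per group = 412 / 1.58 = 260.8.

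- Plan's formula, variance 4 in both arms: power = Φ(d / √(8/260.8) − 1.96), where d = 1 − ratio.
- Log-rate formula: negative binomial matched to mean 1 and variance 4, so k = (4 − 1)/1² = 3. Variance of the log ratio = (1 + 1/ratio + 2k) / 260.8.

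| Ratio | d | Plan's formula | Log-rate formula |
|---|---|---|---|
| 0.51 (the plan's 0.49 reduction) | 0.49 | 80% | 95% |
| 0.59 (point estimate) | 0.41 | 65% | 82% |
| 0.70 (cautious end) | 0.30 | 40% | 51% |

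For 80% power at ratio 0.70, the total would be about 1,640 (log-rate) to 2,205 (plan's formula), against 824.

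**6. Sensitivity, using the difference formula.**

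- Baseline 0.8, 1.2 and 1.3: 28%, 54% and 61% at ratio 0.70; 47%, 80% and 86% at ratio 0.59.
- Variance proportional to the mean (variance/mean = 4): 46% at 0.70 and 75% at 0.59.
- All 450 per group retained: 43% at 0.70 and 69% at 0.59.
- Twelve months of falls (baseline 2; variance 8 if the two half-years are independent, 16 if perfectly correlated): 40% to 68% at 0.70 and 65% to 91% at 0.59.

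**The case against.** The best defence is that the scale is not known. The article says falls drop by 0.59 and never calls it a ratio, and the source that would settle the matter is not at hand. The comparison of readings also has a weakness: variance 4 is used to reject the difference, while the ratio matches only after variance 4 is dropped for Poisson variance. With Poisson variance for both, the readings differ by only 0.01 to 0.03 in the limits, and a difference nearly fits at a baseline of 0.8. The mis-transcribed input could equally be the variance. All of this stands. A reader might infer that the protocol's figures prove 0.59 is a ratio; they make it probable and no more.

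A reader might also infer that the trial reaches 80% power only near the optimistic end. That holds under the difference-in-means formula alone. On the log-rate scale, which is closer to the planned model, power is 82% at the point estimate and 95% to 97% at ratios 0.51 to 0.49.

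It is also fair that data collection runs to 12 months and events are analysed over resident-days at risk, so six-month power may be too low. But with the assumed 12-month variances, power at ratio 0.70 still peaks at 68%.

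Finally, the printed arithmetic is correct, and planning on means for a log-linear analysis is a common approximation. Both are true, but neither resolves the conflict between effect, interval, variance and trial size.

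**Conclusion.** The paragraph is wrong as written. Its effect, interval and variance cannot all describe a mean difference from a trial of 661 residents, given equal arms and a 95% level. That conclusion does not depend on what 0.59 turns out to be.

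That 0.59 is a rate ratio is the most likely explanation, at moderate confidence. If so, the lower limit is the largest effect in the interval, and 80% power at the cautious end is not supported: about 40% to 51% on six-month inputs, and below 80% in every scenario tried. At the point estimate the answer depends on assumptions: 65% to 82% at baseline 1 on six-month falls, and 80% or more with a baseline of 1.2 or higher, or with 12 months of falls at the smallest assumed variance. The figures do not support a general statement that the trial is underpowered at 0.59.

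**What to change.** Check both the scale of 0.59 (0.49 to 0.70) and the variance of four against reference [5].

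- **If it is a rate ratio:** say so under Sample size estimation and remove the implication that the lower limit is the conservative choice. Restate power for the existing sample on the rate-ratio scale of the planned log-linear model, for the follow-up window actually analysed, with the baseline and variance assumptions shown.
- **If it is an absolute difference:** correct the interval or the variance, whichever was mis-stated, and restate the basis of the sample size.

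The cost is one source check and one reworded paragraph. Recruitment need not change. The downside is that the stated power will probably be less favourable.

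### The printed 80% power for falls comes from normal quantiles; with 15 homes per arm and the stated 10% losses it is about 78% at a true 5% level (a minor correction)

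*Protocol article*

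**What the plan says.** The Sample size estimation section takes a published reduction in falls of 0.59 per patient over six months, "with a variance per patient of four", and plans on the cautious value of 0.49: "Using the lower end of this confidence interval". It then states that "261 patients in each group would be required to detect this difference with 80% power and at the 5% level of significance". With an intra-cluster correlation of 0.02 and 30 residents per home, it multiplies by 1.58: "Thus a total of 824 patients (412 in each group) will need to be recruited from approximately thirty homes". Thirty homes of 30 residents are said to leave room for 10% losses.

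The Trial design section fixes 15 homes per arm. On the unit of analysis, the Background says: "Analyses will essentially be at the level of the care home rather than the patient". The Clinical analysis section repeats this. It aggregates falls and days at risk by home, treats homes as random effects, and lists the fixed terms: "Fixed effects in the model will be the intervention itself, the home size (small, medium, large), and resident-type". It says that the standard error of the intervention effect will be adjusted for the cluster design where needed. It does not name the reference distribution for the test.

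**The concern.** A design effect corrects the variance of the treatment comparison. It does not alter how well that variance is known. The intervention varies only between homes, so the error against which it is judged is estimated from about 30 homes, not from some 800 residents. A test that keeps a 5% level on that basis needs a critical value of 2.05 to 2.06 rather than 1.96. The planning calculation uses 1.96.

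The claim at stake is the printed pair, "with 80% power and at the 5% level of significance". If the test respects the small number of homes, power falls below 80%. If it does not, the level rises above 5%. This holds even when all homes are the same size, so it is separate from any variation in home size.

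**Working it through.** **Inputs.** From Sample size estimation: difference 0.49, variance 4, two-sided 5% (sidedness is not stated, but two-sided reproduces the figure), power 80%, intra-cluster correlation 0.02, 30 residents per home, 10% losses. From Trial design: 15 homes per arm.

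**1. The plan's own figure.**
- n per arm = 2 × 4 × (1.960 + 0.842)² / 0.49² = 261.5 (the article gives 261).
- Design effect = 1 + (30 − 1) × 0.02 = 1.58.
- 261 × 1.58 = 412.4 per arm, or 824 in total.

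The article's figures reproduce with normal quantiles.

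**2. Degrees of freedom.** Thirty homes less two arm means leave 28. If home size (2 parameters) and resident type (1) are charged as home-level terms, about 25 remain. The two-sided 5% critical values are 2.048 (28 df) and 2.060 (25 df).

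**3. Power in layouts that match 15 homes per arm.** The standard error is √(2 × 4 × DE / n per arm), and the noncentrality is 0.49 / SE. Power comes from the normal and the noncentral t distributions.

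| Layout | Per home | DE | SE | Normal | t, 28 df | t, 25 df |
|---|---|---|---|---|---|---|
| 405 per arm (900 less 10%) | 27 | 1.52 | 0.1733 | 80.7% | 77.9% | 77.6% |
| 412 per arm over 15 homes | 27.5 | 1.53 | 0.1723 | 81.2% | 78.4% | 78.0% |
| 450 per arm (no losses) | 30 | 1.58 | 0.1676 | 83.2% | 80.6% | 80.2% |

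Like for like, the t reference costs about 3 points. Against the stated 80%, the shortfall at the planned evaluable size is 1.6 to 2.4 points. Without losses, 80% is still reached. The correction therefore uses up most of the margin that the article sets aside for losses.

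**4. Detectable difference.** A noncentrality of 2.90 (28 df) or 2.92 (25 df) gives 80% power. At 405 per arm this is 2.902 × 0.1733 = 0.503 or 2.915 × 0.1733 = 0.505, against the planned 0.49.

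**5. If a normal cut-off were used in the analysis.** The two-sided level would be 2 × P(t > 1.96) = 6.0% (28 df) or 6.1% (25 df).

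**6. Interval width.** 2.048 / 1.960 = 1.045 and 2.060 / 1.960 = 1.051, so a t-based interval is about 5% wider.

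**The case against.** The strongest reply is that nothing in the section is miscalculated. Normal quantiles with a design effect are a common approximation, and the inputs are stated openly. That stands: this is a refinement, not an arithmetic error.

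Several further points also stand, in whole or in part:

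- **Losses.** The falls model uses days at risk as an offset, so residents lost part-way still contribute time. If, as an assumption, they contribute half on average (427.5 per arm, 28.5 per home, DE 1.55), power is 79.3% (28 df) or 79.0% (25 df). The 78% figure takes the article's 10% as lost entirely.
- **Degrees of freedom.** The value of 25 is approximate. Mixed homes supply separate counts for residential and nursing residents, so resident type varies partly within homes. The size and type terms may also explain variance, for which no credit is given here.
- **Planning inputs.** These matter at least as much. An intra-cluster correlation of 0.017 instead of 0.02 restores 80.0% at 405 per arm with 28 df. At the cited point estimate of 0.59, power is about 91%.
- **Model.** The check uses the article's own comparison of two means. It is not a power calculation for the Poisson mixed model that will be fitted.

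A reader might infer two stronger claims. The first is that power is as low as 77%: 412 per arm with a design effect of 1.58 gives 77.1% (28 df) or 76.7% (25 df). That pairing is inconsistent, because 412 residents at 30 per home is 412 / 30 = 13.7 homes per arm, while 28 or 25 df presuppose 15. The second is that the trial will test at a 6% level. The article nowhere names 1.96 or a normal reference for the test. That choice may properly sit in the SAP, so the 6% is a conditional consequence and not an error in the text.

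What none of this removes is that, on the article's own inputs and its own allowance for losses, 80% power and a 5% level do not both hold.

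**Conclusion.** The point holds as a minor correction. At the planned evaluable size of 810 to 824 residents in 30 homes, power for a difference of 0.49 at a true 5% level is about 78% (77.6% to 78.4%), not 80%. It reaches 80% only if nearly all 900 residents contribute fully. This rests on the article's planning model, equal home sizes, an intra-cluster correlation of 0.02, and 25 to 28 degrees of freedom; every value in that range leads to the same conclusion. The documents do not support a power below this range in the planned layout, nor a statement that the type I error will be 6%. The design does not need to change.

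**What to change.** In Sample size estimation, state power as about 78% for a difference of 0.49 after 10% losses, or as 80% for a difference of about 0.505, and say that the calculation uses a t reference based on the number of homes. No extra homes are needed.

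In Clinical analysis or in the SAP, add one sentence: the intervention effect on falls will be tested, and its interval formed, with a small-sample method whose degrees of freedom are based on homes. This guards against the roughly 6% level that a normal cut-off would bring.

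The cost is one restated figure and one sentence, a slightly less favourable power statement, and a confidence interval about 5% wider than with 1.96.
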